### Data Collection and Management

Baseline data will include demographic characteristics (age, sex, BMI), the preoperative QoR-15 score, and comorbidities with diagnostic verification. Intraoperative records will include vital signs, anesthetic agents/dosages, surgical duration, and proportion requiring vasopressor administration. In the postanesthesia care unit, time to extubation, early postoperative Visual Analog Scale pain scores, and incidence of respiratory depression will be documented. Postoperative recovery quality will be assessed at 24 hours by using QoR-15, with 24-hour adverse events systematically recorded. Predefined subgroup analyses stratified by age will be conducted for primary and secondary outcomes, applying identical statistical approaches as specified for the main analyses.

Source data will be documented using standardized case report forms. To minimize data entry errors, independent dual-entry verification will be performed. Physical records will be stored securely in locked cabinets with restricted access within the Department of Anesthesiology. Electronic data will be hosted on encrypted, cloud-based platforms.

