### Sample Size

An initial retrospective review of 10 patients who underwent hysteroscopy under sufentanil-based general anesthesia resulted in a mean QoR-15 score of 129.8 (SD 4.92). Based on published literature, the minimal clinically important difference for QoR-15 is 6 [13]. We hypothesize that oliceridine will improve the postoperative QoR-15 score by this minimal clinically important difference (6 points). Sample size was calculated using PASS 15 software with the following parameters: a standard deviation of 11.5 [13], a 2-sided α of 0.05, and 90% power. The calculation indicated that 48 patients are required per group. To account for an estimated 20% attrition rate, the total sample size was set at 120 patients (60 per group).

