### Statistical Analysis

The primary analysis will be conducted on a modified intention-to-treat population, defined as all randomized participants who receive the study drug (oliceridine or sufentanil) at anesthesia induction. The per-protocol population will consist of modified intention-to-treat participants who complete the 24-hour follow-up assessment without major protocol deviations, serving as the population for supportive analyses. All participants who receive the study drug will be included in the safety analysis set.

Primary/secondary outcomes will be analyzed using SPSS software (version 27.0; IBM Corp), with continuous variables first assessed for normality via Kolmogorov-Smirnov testing; normally distributed data will be expressed as mean (SD), nonnormal data as median (IQR), and categorical variables as counts (%). Quantitative between-group comparisons will employ independent-samples *t* tests or Mann-Whitney *U* tests, while qualitative comparisons will use chi-square, continuity-corrected chi-square, or Fisher exact tests, with all tests being 2-tailed (statistical significance threshold: *P*<.05).

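### The age-subgroup analyses repeat the main two-group tests within strata, and none of these tests whether the treatment effect differs by age

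*Protocol article*

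**What the plan says.** The subgroup commitment is one sentence in the Data Collection and Management section: "Predefined subgroup analyses stratified by age will be conducted for primary and secondary outcomes, applying identical statistical approaches as specified for the main analyses".

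The approaches it points to are in the Statistical Analysis section. For continuous outcomes, "Quantitative between-group comparisons will employ independent-samples" t tests or Mann-Whitney U tests. For categorical outcomes, "qualitative comparisons will use chi-square, continuity-corrected chi-square, or Fisher exact tests, with all tests being 2-tailed", with significance at P<.05. The article names no interaction or heterogeneity test and does not label the subgroups exploratory.

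The planning values are in the Sample Size section. The effect is 6 points on the QoR-15 ("We hypothesize that oliceridine will improve the postoperative QoR-15 score by this minimal clinically important difference (6 points"), with "a standard deviation of 11.5 [13], a 2-sided α of 0.05, and 90% power". The section then states that "The calculation indicated that 48 patients are required per group", raised to 60 per group for 20% attrition.

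**The concern.** What an age subgroup adds to the main analysis is an answer to whether the treatment effect varies with age. A test of oliceridine against sufentanil among younger patients, followed by the same test among older patients, does not address this. A P value below .05 in one stratum and above it in the other is weak evidence of a difference between them, because each stratum is small and its P value depends heavily on its size.

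The sentence covers the primary outcome and all seven secondary endpoint items, under one significance threshold. At stake is how the subgroup results are interpreted: a pattern in which the drug appears to help one age group and not the other could be taken for a finding when it is only what low power produces. The primary comparison itself is not affected.

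**Working it through.** **Inputs.** Effect 6 points, SD 11.5, two-sided α 0.05, 48 or 60 per arm (Sample Size); 1:1 allocation (Randomization and Blinding). *Assumptions:* two age strata, the same split in both arms, split ranging from 50:50 to 80:20. The article gives no age bands, so the range is shown.

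**The plan's own figure.** n per group = 2(1.960 + 1.282)² × 11.5² / 6² = 77.2, so 78 (79 with the t distribution). The stated 48 does not follow from the stated inputs. The attrition step does: 48/0.8 = 60. This is a separate matter and the present point does not depend on it. It does mean that overall power is about 72% at 48 per arm and 81% at 60, so the strata start from a lower base than 90%.

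**Step 1: power within a stratum.** Standardised effect d = 6/11.5 = 0.5217. With m patients per arm in the stratum, power comes from the noncentral t distribution with noncentrality d√(m/2) and 2m − 2 degrees of freedom.

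**Step 2: chance that exactly one stratum is significant** when the effect is 6 points in both: p₁(1 − p₂) + p₂(1 − p₁).

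| Per arm | Split | p₁ | p₂ | Exactly one significant |
|---|---|---|---|---|
| 60 | 50:50 | 0.511 | 0.511 | 0.500 |
| 60 | 60:40 | 0.588 | 0.425 | 0.513 |
| 60 | 70:30 | 0.656 | 0.331 | 0.553 |
| 60 | 80:20 | 0.716 | 0.231 | 0.616 |
| 48 | 50:50 | 0.425 | 0.425 | 0.489 |
| 48 | 60:40 | 0.494 | 0.350 | 0.498 |
| 48 | 70:30 | 0.558 | 0.271 | 0.527 |
| 48 | 80:20 | 0.617 | 0.191 | 0.572 |

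Example, 60 per arm at 80:20: 0.716 × 0.769 + 0.231 × 0.284 = 0.551 + 0.066 = 0.616 (fractional stratum sizes are kept where they arise).

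**Step 3: no effect at any age.** 2 × 0.05 × 0.95 = 0.095 per outcome.

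**Step 4: what an interaction test does instead.** In simulation (20,000 trials per scenario, normal data, SD 11.5, strata of 30/30, 42/18, 48/12 and 24/24 per arm), a test of the difference between the two stratum effects was significant in 4.7% to 5.2% of trials, whether the common effect was 0 or 6 points. The same simulations gave split results in 49% to 62% of trials under a uniform 6-point effect and in 9.5% to 9.6% under none, matching steps 2 and 3.

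**Step 5: power of the interaction test.** The standard error of the difference between stratum effects is 11.5 × √(2/m₁ + 2/m₂). At 60 per arm:
- 50:50: 11.5 × √(2/30 + 2/30) = 4.20. Power for a 6-point difference is 29.8%; 80% power needs 2.80 × 4.20 = 11.8 points.
- 80:20: 11.5 × √(2/48 + 2/12) = 5.25. Power is 20.8%; 80% power needs 14.7 points.

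These powers are for a two-stratum contrast. Power with age kept continuous depends on the age distribution, which the article does not give.

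**The case against.** The strongest reply is that the subgroup sentence says only how arms are compared within strata. It does not rule out a heterogeneity test, and a statistical analysis plan that is not shown could add one. That is possible, but the article does more than stay silent: it states the method and ties it to the main-analysis tests, none of which can address effect modification. A plan that follows that sentence literally would have no such test.

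Three stronger readings are tempting, and the documents do not support them.

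- *That the age bands are open and could be chosen after seeing the data.* The article calls the analyses predefined, and a journal article may leave the bands to the full protocol. Nothing shows that they are unfixed.
- *That a split result is the expected outcome.* With two equal strata of equal power, 2p(1 − p) cannot exceed 50%, so it is at most an even chance. It passes one half only when the strata are sufficiently unequal, and it falls to about 9.5% per outcome if there is no effect.
- *That a false claim of benefit in one age group is likely, or would be reported.* The objective and conclusions concern the overall comparison only, and no age hypothesis is stated. The figures are probabilities of discordant P values; these mislead only if someone reads them as an age difference.

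It is also fair to say that an interaction test will seldom detect a plausible difference in a trial this size. That argues for reporting an estimate with its interval, not for separate tests.

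**Conclusion.** The point holds in a limited form. The stated method cannot test whether the effect of oliceridine varies with age. If the planned 6-point effect is the same at all ages, it gives a result significant in exactly one of two strata in about 49% to 62% of trials, against about 5% false positives for an interaction test. With no effect at any age, the split occurs in about 9.5% of trials per outcome.

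These figures rest on two strata, normal data, SD 11.5 and splits from 50:50 to 80:20; the number of strata and the split are assumptions. The primary analysis and the trial's main conclusion are unaffected. The risk is confined to misreading the subgroup results, and the plan as written contains no guard against it. It should be corrected because the correction is cheap.

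**What to change.** Replace the subgroup sentence with wording such as:

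> Effect modification by age will be assessed for the primary outcome by a treatment-by-age interaction in a linear model containing treatment, age and their product. The interaction will be reported as an estimate with 95% CI and P value. Age-subgroup analyses are exploratory. Treatment effects within age strata will be given as estimates with confidence intervals, and no difference between age groups will be claimed from within-stratum P values.

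Preoperative QoR-15 may be added to the model because it is already collected at baseline, but the fix does not depend on it.

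**Cost.** One additional model beyond the two-group tests now planned, which with continuous age assumes that the treatment effect changes linearly with age. No new data are needed, and sample size, conduct and the primary analysis stay as they are. The main limitation is low power, about 21% to 30% at 60 per group for a 6-point difference between strata. A nonsignificant interaction must therefore not be read as evidence that the effect is the same at all ages. The change should be documented before any unblinded analysis.

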### Data Reporting Guidelines

The SPIRIT (Standard Protocol Items: Recommendations for Interventional Trials) reporting guidelines will be used for this paper (Multimedia Appendix 1).

### Sample Size

An initial retrospective review of 10 patients who underwent hysteroscopy under sufentanil-based general anesthesia resulted in a mean QoR-15 score of 129.8 (SD 4.92). Based on published literature, the minimal clinically important difference for QoR-15 is 6 [13]. We hypothesize that oliceridine will improve the postoperative QoR-15 score by this minimal clinically important difference (6 points). Sample size was calculated using PASS 15 software with the following parameters: a standard deviation of 11.5 [13], a 2-sided α of 0.05, and 90% power. The calculation indicated that 48 patients are required per group. To account for an estimated 20% attrition rate, the total sample size was set at 120 patients (60 per group).

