### Randomization and Blinding

Block randomization with block sizes of 4 or 6 will be performed using a computer-generated sequence. An independent researcher not involved in the trial will prepare sequentially numbered, opaque, sealed envelopes containing group assignments. Participants will be allocated in a 1:1 ratio to either the experimental or control group by opening these envelopes in a sequential order at the time of enrollment. Allocation cards will be sealed inside opaque envelopes to ensure concealment. The study medications (oliceridine or sufentanil) will be prepared by a dedicated research nurse as visually identical clear solutions in 10-mL syringes. These prepared syringes will then be provided to the anesthesiologist, who will remain unaware of the treatment allocation. Blinding will be maintained for the participants, the anesthesiologist, and the outcome assessors throughout the trial to minimize assessment bias. The blinding will be broken only in the event of severe adverse events. Study participants, their legally authorized representatives, the anesthesiologist, and outcome assessors will be blinded to group allocation throughout the trial. Unblinding the allocation is generally not required per protocol. Emergency unblinding will be performed exclusively to determine rescue medications for critical adverse events or during other medical emergencies

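### The listed sample-size inputs (6 points, one SD of 11.5, two-sided 5%, 90% power) require 79 patients per group, not 48; if the SD is 11.5 in both arms, power is about 72% to 81%

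*Protocol article*

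**What the plan says.** The Sample Size section gives a complete set of inputs for a comparison of two means:

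- **Difference:** the hypothesised gain with oliceridine is the minimal clinically important difference, 6 points on QoR-15.
- **SD in the list of PASS 15 parameters:** "a standard deviation of 11.5 [13"], one value, with no separate figure for each arm.
- **Error rates:** "a 2-sided α of 0.05, and 90% power".
- **Result:** "The calculation indicated that 48 patients are required per group".
- **Attrition:** 20%, which takes the total to 120 (60 per group).

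The same paragraph opens with a retrospective review of 10 sufentanil patients with a mean QoR-15 of 129.8 and an SD of 4.92. That SD is not among the listed parameters.

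Elsewhere, Randomization and Blinding fixes 1:1 allocation. Statistical Analysis states the test: "Quantitative between-group comparisons will employ independent-samples *t* tests or Mann-Whitney *U* tests", two-tailed at 5%.

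**The concern.** All the inputs and the result are printed together, so the calculation can be repeated directly, and it does not reproduce. The stated 48 is 39% below the 79 that the listed inputs require (1 − 48/79 = 0.39), which is too large a gap for rounding or for a difference between software packages. Nor is this a detail that a condensed article leaves to a fuller document, because the inputs and the result contradict each other in one paragraph.

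This paragraph is the only power justification for the primary outcome. If its 90% is too high, the risk of missing a true effect as large as the minimal clinically important difference is greater than the stated 10%, and a reader of the final report would weigh a non-significant result against the wrong figure.

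**Working it through.** **Inputs** (Sample Size section unless noted): difference δ = 6; SD σ = 11.5; two-sided α = 0.05; power 90%; 1:1 allocation (Randomization and Blinding); two-sample t test (Statistical Analysis).

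**1. Required n with a common SD of 11.5.**
Normal approximation: n = 2(1.960 + 1.282)²(σ/δ)² = 2 × 10.507 × (11.5/6)² = 2 × 10.507 × 3.674 = 77.2, so 78 per group.
Exact noncentral t, standardised difference 6/11.5 = 0.522: n = 78.17, so **79 per group**. The plan states 48.
At a Mann-Whitney relative efficiency of 0.955 under normality, the requirement is 78.17/0.955 = 81.9, so 82.

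**2. Attrition step.** 48/0.8 = 60 per group, 120 in total. This reproduces, so the discrepancy lies in the 48.

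**3. Power for 6 points with a common SD of 11.5.**

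| Evaluable per group | SE = 11.5√(2/n) | 6/SE | Power, normal | Power, exact t |
|---|---|---|---|---|
| 48 (20% attrition) | 2.347 | 2.556 | 72.4% | 71.6% |
| 60 (no attrition) | 2.100 | 2.858 | 81.5% | 80.9% |

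The type II error is therefore about 28% or 19%, against the stated 10%.

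**4. Can 48 be recovered from other inputs?**

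| Variant | n per group | Agrees with the listed inputs? |
|---|---|---|
| SD 4.92 in both arms | 15 to 16 | No |
| One-sided 0.05, 80% power, SD 11.5 | 46 to 47 | No: sidedness and power differ |
| One-sided 0.10, 90% power, SD 11.5 | 49 | No: sidedness and alpha differ |
| Welch t test, SDs 4.92 and 11.5 | **48** | Difference, alpha and power agree; two SDs are not described |

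For the last row, at n = 48: SE = √[(4.92² + 11.5²)/48] = √(156.46/48) = 1.805 and 6/SE = 3.323. With about 63.6 Welch degrees of freedom, power is 90.5%. At n = 47 it is 89.9%. The smallest n that reaches 90% is therefore exactly 48. With equal group sizes the result is the same whichever arm has the smaller SD. Assigning 4.92 to sufentanil follows from the pilot patients having received sufentanil.

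With a single common SD, 48 per group reaches 90% power only if that SD is about 8.97, a value that is printed nowhere. If the SD stays at 11.5, the difference would have to be about 7.7 points.

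**5. How firm is 4.92?** For 10 patients, under normality, the 95% interval for the SD is 4.92√(9/19.02) to 4.92√(9/2.70), about 3.4 to 9.0. With 9.0 in one arm and 11.5 in the other, SE at n = 48 is √[(9.0² + 11.5²)/48] = 2.11, 6/SE is 2.85, and power is about 80%.

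**The case against.** The strongest defence is that 48 is not a slip. Every number needed to obtain it is printed in the Sample Size section: the pilot SD of 4.92 belongs to the control drug, 11.5 is the literature value, and an unequal-variance calculation with the two gives 48 exactly. On that reading the sample size is correct for its inputs, and the fault is an incomplete report of them. The exact match carries weight, and it means that the pilot SD cannot be dismissed as unrelated to the 48.

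It does not clear the paragraph. Only 11.5 appears in the list of parameters, and neither unequal variances nor a Welch procedure is mentioned. No reason is given why QoR-15 should be more than twice as variable under oliceridine as under sufentanil (11.5/4.92 = 2.3). The match is an inference about what was done, not something the protocol states.

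A second objection is that follow-up for the primary outcome lasts only 24 hours, so attrition may fall well below 20%. That is fair. It moves the common-SD power towards 81%, which is still short of 90%.

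A reader might also infer that a non-significant result will be reported as evidence of no benefit. The protocol frames a superiority hypothesis and plans no such interpretation, so that is a risk of overstated power and not something the plan commits to.

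**Conclusion.** The point holds as an inconsistency in the protocol: the inputs as listed require 79 per group, and neither the 48 nor the 90% follows from them.

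The size of the power shortfall is conditional. If the SD is 11.5 in both arms and the true difference is 6 points, t-test power is about 72% with 48 evaluable per group and about 81% with 60. If the calculation used 4.92 and 11.5, then 48 gives 90.5% on those inputs, but the inputs are misreported and the claim depends on an SD from 10 retrospectively reviewed patients in one arm.

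A reader might conclude outright that the trial has 72% power. The document does not support that as a fact, because it cannot settle which SDs were entered or what the true SDs are, and the 72% also assumes the full 20% attrition. Either the listed inputs or the stated sample size is wrong, and the paragraph must be corrected in both cases.

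**What to change.** State the SD used for each arm and the PASS procedure that was run. Then:

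- **If a common SD of 11.5 applies:** replace the 90% power statement. For 120 randomised and a 6-point difference, power is about 72% with 20% attrition and about 81% with none.
- **If unequal SDs were used:** report both with their sources, justify the difference between arms, and give the power under a common SD of 11.5 (the same 72% to 81%) as a sensitivity figure.

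Carry the corrected statement into the final report. It needs no outcome data and no change in enrolment; for scale only, 79 evaluable per group with 20% attrition would be 79/0.8 = 98.75, so 99 per group and 198 in total. The cost is a rewritten paragraph and, under a common SD, a less favourable stated power.

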### Recruitment Plan

Based on institutional surgical volume projections, patient recruitment is scheduled to commence in July 2025 and is anticipated to be completed within a 5-month period to enroll the target cohort of 120 participants. Eligible patients will be identified primarily through active screening of institutional surgical schedules for planned hysteroscopies. Preoperative screening for eligible candidates will be conducted by the investigators. Written informed consent will be obtained from all participants or their legally authorized representatives either before or on the day of surgery. The consent process, approved by the institutional review board, ensures comprehensive disclosure of the potential benefits, risks, and alternative treatments. Documentation will confirm that all participants have fully understood the information before providing their signature.

### Statistical Analysis

The primary analysis will be conducted on a modified intention-to-treat population, defined as all randomized participants who receive the study drug (oliceridine or sufentanil) at anesthesia induction. The per-protocol population will consist of modified intention-to-treat participants who complete the 24-hour follow-up assessment without major protocol deviations, serving as the population for supportive analyses. All participants who receive the study drug will be included in the safety analysis set.

Primary/secondary outcomes will be analyzed using SPSS software (version 27.0; IBM Corp), with continuous variables first assessed for normality via Kolmogorov-Smirnov testing; normally distributed data will be expressed as mean (SD), nonnormal data as median (IQR), and categorical variables as counts (%). Quantitative between-group comparisons will employ independent-samples *t* tests or Mann-Whitney *U* tests, while qualitative comparisons will use chi-square, continuity-corrected chi-square, or Fisher exact tests, with all tests being 2-tailed (statistical significance threshold: *P*<.05).

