### Outcomes

The primary outcome is defined as the quality of postoperative recovery at 24 hours after surgery and will be assessed using QoR-15 (score range: 0-150; higher scores indicate better recovery). Secondary efficacy endpoints are (1) hemodynamic changes during induction (mean arterial pressure/heart rate at T0 [pre-drug], T1 [pre-LMA], T2 [post-LMA immediate], T3 [5-min post-LMA]); (2) total intraoperative opioid consumption and supplemental bolus frequency; (3) proportion requiring vasoactive agents; (4) incidence of postanesthesia care unit respiratory depression (defined as respiratory rate <6 bpm, end-tidal carbon dioxide amplitude change >50 mm Hg or <30 mm Hg, or waveform loss >20 s); (5) time to extubation; (6) opioid-related adverse events within 24 hours; and (7) Visual Analog Scale pain scores at 30 minutes, 4 hours, 8 hours, and 24 hours postextubation.

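### The primary QoR-15 comparison makes no use of the preoperative QoR-15, giving up precision in a trial that falls short of its stated power

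*Protocol article*

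**What the plan says.** The Outcomes section sets the endpoint: "The primary outcome is defined as the quality of postoperative recovery at 24 hours after surgery and will be assessed using QoR-15", on a 0-150 scale. Under Data Collection and Management the baseline data include "the preoperative QoR-15 score, and comorbidities with diagnostic verification", and Table 1 places baseline data in the enrollment phase. The same scale is therefore due to be measured before surgery and at 24 hours.

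The Statistical Analysis section covers primary and secondary outcomes together. After a Kolmogorov-Smirnov check of normality, "Quantitative between-group comparisons will employ independent-samples" t tests or Mann-Whitney U tests. It names no covariate, no ANCOVA and no change score. The age subgroup analyses are to use the same methods as the main analyses, so they do not use the baseline score either.

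The Sample Size section assumes a 6-point difference with "a standard deviation of 11.5 [13], a 2-sided α of 0.05, and 90% power" and concludes: "The calculation indicated that 48 patients are required per group". Allowance for 20% attrition brings this to 60 per group.

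**The concern.** A preoperative score on the outcome scale is usually among the better predictors of the postoperative score. If it predicts at all, putting it in the model removes part of the between-patient variance from the treatment comparison. It also corrects the estimate for whatever baseline difference happens to arise. The protocol plans to collect this score and then leaves it out of every stated comparison.

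In a generously sized trial this would be a minor point. Here the stated sample size does not deliver the stated power, and recruitment was well advanced when the article was written (55 enrolled as of September 2025, completion anticipated by December 2025). Precision available from data already scheduled is therefore worth having. At stake is a larger than intended chance of missing a true 6-point benefit, and a wider confidence interval than necessary.

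**Working it through.** **Inputs from the protocol.** Difference 6 points; SD 11.5; two-sided alpha 0.05; power 90%; 48 evaluable and 60 randomized per group; 1:1 allocation.

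**Input not in the protocol.** The correlation r between preoperative and 24-hour QoR-15. It is an assumption, shown over a range.

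**Step 1: the plan's own figure.** With the normal approximation, n per group = 2 × (1.960 + 1.282)² × 11.5² / 6² = 77.2, rounded up to 78. The exact noncentral-t calculation gives 79. The stated 48 is not reproduced. The attrition step is right: 48 / 0.8 = 60.

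**Step 2: power of the unadjusted test.** The standard error of the difference is 11.5 × √(2/n).
- 48 per group: SE = 2.35; 6 / 2.35 = 2.56; power 72.4% (normal) or 71.6% (exact t).
- 60 per group: SE = 2.10; 6 / 2.10 = 2.86; power 81.5% (normal) or 80.9% (exact t).

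**Step 3: power after adjusting for baseline.** The residual SD is 11.5 × √(1 − r²), so residual variance falls by r². Exact-t results, ignoring the one degree of freedom spent on the covariate (negligible with 96 to 120 patients):

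| Assumed r | Variance removed | Residual SD | Power, 48 per group | Power, 60 per group | n per group for 90% |
|---|---|---|---|---|---|
| 0 (as planned) | 0% | 11.50 | 71.6% | 80.9% | 79 |
| 0.2 | 4% | 11.27 | 73.3% | 82.5% | 76 |
| 0.3 | 9% | 10.97 | 75.6% | 84.4% | 72 |
| 0.4 | 16% | 10.54 | 78.8% | 87.1% | 66 |
| 0.5 | 25% | 9.96 | 83.2% | 90.5% | 59 |
| 0.6 | 36% | 9.20 | 88.5% | 94.3% | 51 |
| 0.7 | 49% | 8.21 | 94.3% | 97.8% | 41 |

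Reaching 90% needs r of about 0.63 with 48 evaluable per group, or about 0.49 if all 60 are evaluable.

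**Step 4: chance imbalance.** The randomization section describes blocks of 4 or 6 and mentions no stratification by baseline score. If the preoperative SD were also 11.5 (an assumption), the baseline difference between groups would have a standard error of 2.35 points at 48 per group and 2.10 at 60. With r = 0.5 and equal SDs, an imbalance of one standard error at 48 per group would move the unadjusted difference by about 0.5 × 2.35 = 1.2 points, a fifth of the 6-point target.

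**The case against.** The strongest reply is that nothing here is wrong. Under randomization the unadjusted comparison is unbiased and holds its error rate, and that error rate already allows for chance imbalance. This is correct: the loss is of efficiency, and of accuracy given the imbalance actually observed, not of validity.

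Second, the article is condensed and an unseen analysis plan might add adjusted models. That limits certainty about supplementary analyses. But the article names the between-group tests for the primary outcome, so an adjusted primary analysis would contradict it. The point challenges a stated choice, not a gap.

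Third, the gain depends on a correlation that the documents do not give. This stands as a limit on size: at 0.2 the gain is under 2 percentage points. At no value in the table does adjustment lower power.

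Fourth, the protocol's retrospective review of 10 patients gave an SD of 4.92. If that were the true SD, 48 per group would have over 99.9% power for 6 points and adjustment would add almost nothing to power. But the protocol did not use that SD in its calculation, and ten patients are a weak basis for one.

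Fifth, the sample-size shortfall is a separate defect, and adjustment closes it at 48 per group only if r is about 0.63 or more. That is right: the shortfall explains why lost precision matters here and should not be counted twice.

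Finally, a late change to the primary analysis of a registered trial needs formal documentation. This also stands and is taken up in the fix.

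**Conclusion.** The point holds. The protocol schedules the preoperative QoR-15, fixes an unadjusted test for the 24-hour score and uses the baseline value in no comparison. With its own difference and SD, power is about 72% at 48 evaluable per group and 81% at 60. Adjustment would bring this to 76-89% and 84-94% respectively for an assumed correlation of 0.3 to 0.6. Those gains rest on that correlation, on the SD of 11.5 and on near-complete baseline scores, which the protocol plans for but cannot guarantee. This is an improvement that should be made, not a flaw that invalidates the trial. It only partly repairs the power shortfall.

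**What to change.** Make the primary analysis a linear model (ANCOVA) of the 24-hour QoR-15 on treatment group, with the preoperative QoR-15 as covariate, in the modified intention-to-treat population. Report the adjusted mean difference with its 95% confidence interval and P value.

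The amendment should also settle three details:
- The adjusted model stays primary whatever the Kolmogorov-Smirnov result, so that the estimate remains on the scale of the 6-point difference. The unadjusted t test or Mann-Whitney test becomes a sensitivity analysis.
- State how a missing preoperative score is handled, so that no patient is lost from the analysis for lack of a covariate.
- State how the model is checked if the bounded score proves skewed, for example with robust or bootstrap standard errors.

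Date the amendment, record it with the registry and ethics committee, and complete it before anyone sees outcome data by group. A choice made later would look data-driven.

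The cost is a change of wording and the amendment paperwork. No new assessment is needed, and SPSS fits the model. The sample-size statement still needs its own correction, and any credit it takes for baseline adjustment should rest on a justified correlation.
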